### General treatment regimen

After confirmation of the correct position of the feeding tube, enteral nutrition is initiated and increased to the required amount as advised by the treating physicians, whenever possible after consulting a dietitian. The dietitian can advise on a schedule for the resumption of oral feeding during enteral nutrition. When enteral nutrition is no longer indicated (i.e. oral intake exceeding 50% of the patient’s daily required caloric intake with an upward trend), it is ceased and the feeding tube is removed. These decisions are not influenced by the method by which the enteral feeding tube was placed.

In patients with symptoms of dislodgement (e.g. nausea, vomiting or reflux of tube feeding via the nasogastric tube), dislodgement of the nasoenteral feeding tube will be confirmed on abdominal radiograph or Cortrak® monitor (by reinsertion of the stylet). In patients with blockage of the tube (i.e. inability to pass tube feeding through the tube), an attempt will be made to resolve the clogging by flushing of the tube with water or acetylcysteine. In case of confirmed dislodgement or irreversible blockage of the tube, replacement (or repositioning if possible) will be performed with the allocated technique, except after conversion from EM guidance to endoscopy after failed initial EM guided placement. Prokinetic agents (e.g. metoclopramide or erythromycin) can be used according to the preference of the treating physician.

Patients are discharged when considered appropriate by the treating team. In select cases, patients can be discharged with the feeding tube in situ to continue enteral nutrition at home or a nursing home. In such cases, the care for enteral nutrition is taken over by (nursing) homecare. Any problems with the tube are taken care of in the outpatient clinic for as far as possible.

### Primary outcome

The primary outcome is the need for reinsertion of the feeding tube, defined as the insertion of an endoscope or tube in the nose/mouth and esophagus for (re)placement of the feeding tube. This outcome reflects the feasibility of the technique itself as well as the need for repeated procedures due to tube-related complications. Tubes will be reinserted when there is an ongoing indication for enteral feeding (as advised by the consulting dietitian) after initial unsuccessful placement, dislodgement or blockage of the tube. Endoscopic placement after failed initial EM guided attempt (crossover) is also considered a reinsertion. Repositioning guided by the EM transmitting stylet is not considered a reinsertion as long as the tube has not left the stomach/esophagus.

### Secondary outcomes

EM guided placement of a nasoenteral feeding tube is hypothesized to be less discomforting to the patient compared to endoscopic placement, at lower costs. Secondary outcomes therefore include: patient-reported outcomes (e.g. pain, discomfort, and total burden) and costs of both tube placement procedures. The costs will include the direct and indirect medical costs of initial tube placement (including personnel, materials, sedation, equipment and transport), tube related complications, diagnostic investigations, and feeding related interventions.

Other secondary outcomes are: the success rate of tube placement; duration of the tube placement procedure; time between physician order and tube placement and start of feeding; time to reach the feeding goal; all feeding related interventions (including EM guided repositioning without reinsertion of the tube) with corresponding indication; duration of tube stay; tube (placement) related complications (such as dislodgement, blockage, epistaxis, aspiration); use of parenteral nutrition; length of hospital stay; and in-hospital mortality (see Table 1 for definitions).

**Table 1 Tab1:** **Definitions of outcomes**

**Outcome**	**Definition**
Reinsertion	The insertion of an endoscope or tube in the nose/mouth and esophagus for (re) placement of the feeding tube.
Repositioning	Reinsertion of the EM transmitting stylet when the tube has not left the stomach/esophagus.
Dislodgement	Any displacement of the feeding tube making continuation of tube feeding unsafe (e.g. because it is delivered into the stomach in the presence of gastroparesis) or impossible (e.g. when the tube has been removed from the patient), confirmed on the Cortrak® monitor or abdominal radiograph.
Blockage	The inability to pass tube feeding through the tube whilst it is still in the correct position.
Successful tube placement	The tip of the feeding tube positioned beyond D2 [preferably near the ligament of Treitz (i.e. duodenojejunal flexure)] or in the efferent jejunal limb (in the presence of a gastro- or duodenoenterostomy) on the Cortrak® monitor or abdominal radiograph (depending on the placement method) followed by successful enteral feeding, without signs of feeding entering the stomach.
Duration of tube stay	The number of days that the feeding tube was in its correct position.

### Data collection and follow-up

Clinical data with regard to baseline characteristics and outcomes will be collected during hospital admission using written standardized case report forms (CRFs) (Figure 3). The CRFs will be completed by the local treating physicians or the study coordinator. The CRFs will be checked with source data by the primary and/or secondary study coordinator. The utilization of healthcare in terms of direct medical costs of initial tube placement, sedation, tube-related complications, diagnostic investigations, and feeding related interventions will be registered as part of the data collection for the trial.

**Figure 3 Fig3:**
[figure not shown]
**CORE trial flow chart of eligibility and group allocation.**

Patients will be asked to complete a short questionnaire after each tube (re)placement procedure. The questionnaire will consist of a visual analogue scale (VAS) scoring sheet, for the dimensions discomfort, pain, social embarrassment, anxiety, and total burden (comparable to the study by Deutekom *et al*. [16]). In addition, patients will also be asked what their advice would be to a friend or colleague in the same situation. Patients randomized to EM guided tube placement with past experiences with endoscopic tube placement and vice versa will additionally be asked for their preference for one or the other tube placement method.

Patients are followed for as long as they are hospitalized and during any outpatient clinic or day-care visit related to the feeding tube (see Additional file 1 for the time schedule of enrolment, interventions, and assessments).

### Safety

All physicians involved in the study will be instructed to contact the coordinating investigator in case of mortality or tube (placement) related unexpected adverse events leading to prolonged hospitalization. All severe adverse events that may be related to the feeding tube or placement procedure and all cases of mortality will be reported to the Central Committee on Research involving Human Subjects (in Dutch: Centrale Commissie Mensgebonden Onderzoek) and the Institutional Review Board using an online module [17]. Due to the perceived negligible risk associated with participation in this study, monitoring by a Data Safety Monitoring Board is not required according to Dutch legislation.

### Ethics

The study will be conducted according to the principles of the Declaration of Helsinki (59th version, October 2008) and in accordance with the Dutch Medical Research Involving Human Subjects Act (WMO). The independent ethics review board of the Academic Medical Center (Amsterdam, the Netherlands) has approved the study protocol. Secondary approval was obtained from the boards of the Canisius Wilhelmina Hospital, Gelre Hospital, Hospital Gelderse Vallei, and University Medical Center Utrecht according to the Dutch CCMO External Review Directive 2012 (RET 2012). Written informed consent will be obtained from all participating patients prior to randomization. The trial is registered in the Dutch Trial Register (http://www.trialregister.nl/trialreg/index.asp) with identification number NTR4420.

### Statistical aspects

#### Sample size calculation

The CORE trial is designed as a non-inferiority trial, hypothesizing that the need for reinsertion of a nasoenteral feeding tube after EM guided placement is at most 10% worse as compared to endoscopic placement.

Sample size is calculated based on data from previous studies and experiences from our pilot study.

Success is defined the absence of the need for reinsertion of an endoscope or tube. We estimate a success rate of 78% in the EM guided group versus 70% in the endoscopic group. When the non-inferiority limit is set at 10%, significance level at 0.05 and power at 80%, the sample size required per study arm is 73 [18]. Taking into account a 5% loss to follow-up rate (based on previous studies), a total of 154 patients will have to be randomized in this study.

#### Descriptive statistics

For dichotomous data, frequencies will be presented. Continuous data will be presented as means and standard deviations or medians and interquartile ranges, depending on their distribution. Baseline characteristics (all prior to randomization) include: age, sex, body mass index, American Society of Anesthesiologists (ASA) physical status, indication for hospital admission, type of surgery (if applicable), indication for enteral nutrition, cause of gastroparesis (if applicable), interval between surgery and primary tube placement, use of prokinetic agents and presence of an altered upper GI anatomy after previous surgery.

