### Randomization

Eligible patients will be recruited on the clinical ward by the principal investigators or a designated substitute. After obtaining informed consent, patients will be randomized centrally by the study coordinator using an online randomization module (Clinical Research Unit, Academic Medical Center, Amsterdam, the Netherlands) in a 1:1 ratio between EM guided and endoscopic tube placement (Figure 1).

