### Group A: Electromagnetic guided nasoenteral feeding tube placement

The feeding tube (Corflo® nasojejunal feeding tube, Corpak Medsystems, Wheeling, Ill, US) is placed by a trained nurse at the patient’s bedside on the clinical ward, with the patient in a supine position. If a nasogastric decompression tube is in place, it is advised, but not mandatory, to empty the stomach and remove the nasogastric tube before proceeding. Preprocedural fasting is not required. By using an electromagnetic transmitting stylet, the nurse can follow the path of the tip of the feeding tube on a monitor screen (Cortrak® Enteral Access System, Corpak Medsystems, Wheeling, Ill, US) (Figure 2). The stylet at the tip of the feeding tube transmits its signal to a receiver unit placed at the patient’s epigastric region. Both the stylet and the receiver unit are attached by a cable to the monitor unit, which provides a graphic display of the feeding tube tip location and the followed track. In the anterior view, the tube can be followed on its way through the esophagus, stomach, duodenum, and jejunum. In the depth cross-section, the passage of the tube from the pylorus into the duodenal bulb and the second part of the duodenum can be seen. The tube is advanced to a post-pyloric position, preferably near or beyond the duodenojejunal flexure. Adequate positioning is assessed by the path of the tube on the screen. Subsequently, the transmitting stylet is removed from the feeding tube. Finally, the tube is secured to the nostrils with tape. Abdominal radiographs are not used, as the Cortrak® Enteral Access System was shown to correlate with abdominal radiography in 99.5% of cases and is cleared by the Food and Drug Administration (FDA) for feeding tube placement confirmation [9,11]. The stylet is kept at the patient’s bedside in case repositioning of the nasoenteral tube is required. The procedure is abandoned if the tip of the tube has not passed the pylorus after 30 minutes. In case of failure of EM guided placement, patients allocated to EM guided bedside placement will undergo endoscopic placement. According to the intention-to-treat principles these patients will be analyzed in the EM guided group.

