### Group B: Endoscopic nasoenteral feeding tube placement

Endoscopy is performed by trained gastroenterologists (or supervised gastroenterologists in training) assisted by one or two endoscopy nurses in the endoscopy department. Patients fast from midnight but clear fluids are allowed up to 3 hours before the procedure. Conscious sedation is used if indicated (e.g. requested by the patient). A nasal or oral endoscope is introduced into the duodenum or jejunum. According to the gastroenterologist’s preference, the feeding tube is either pulled along with the endoscope, advanced through the endoscope or advanced over a guide wire and placed as far as possible in the duodenum or jejunum. Finally, the tube is secured to the nostrils with tape. Within 3 hours after tube placement, an abdominal radiograph is performed and reviewed by an independent radiologist who is not involved in the study. In case of incorrect feeding tube placement, repeat endoscopic tube placement is performed. In case of second placement failure, the study is terminated for that patient and an alternative feeding strategy (but not EM guided placement) is used according to the preference of the treating physician.

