#### Analyses

All analyses will be according to the intention-to-treat principles, meaning that all randomized patients are included in their initially assigned study arm, regardless of adherence to study protocol. The primary and secondary outcomes will be compared between the treatment groups. Results are presented as risk ratios with corresponding 95% confidence intervals. Except for the primary analysis of non-inferiority, a difference with a two-tailed P < 0.05 is considered statistically significant. In the event of imbalance between the two study arms a multivariable logistic regression will be used to correct for possible confounders. Additional as-treated and per-protocol analyses will be performed for the primary endpoint and the success rate of both tube placement methods.

A predefined subgroup analysis will be performed in patients with and without an altered upper GI anatomy after previous surgery. We will use logistic regression models to perform a formal test for interaction to assess whether outcomes differed significantly between these subgroups.

Interim analysis to evaluate serious adverse events and potentially prematurely terminate the study will not be performed, because of the perceived negligible risk associated with participation in this study.

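### A variable listed as pre-randomization, the time from surgery to primary tube placement, ends at the allocated procedure, so it may carry an effect of allocation into the baseline table and any adjusted analysis

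*Protocol article*

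**What the plan says.** The Descriptive statistics section of the protocol article opens its list with "Baseline characteristics (all prior to randomization) include" and includes in it "interval between surgery and primary tube placement".

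The Randomization section puts allocation before the procedure: "After obtaining informed consent, patients will be randomized centrally by the study coordinator using an online randomization module". What is allocated is the method of tube placement.

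The arms differ in what comes before placement. For Group A, placed at the bedside: "Preprocedural fasting is not required". For Group B, placed in the endoscopy department: "Patients fast from midnight but clear fluids are allowed up to 3 hours before the procedure".

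Secondary outcomes include "time between physician order and tube placement and start of feeding".

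The Analyses section adds a conditional adjustment: "In the event of imbalance between the two study arms a multivariable logistic regression will be used to correct for possible confounders". It names no covariates and gives no criterion for imbalance.

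**The concern.** A baseline characteristic should be fixed before allocation, so that any difference between arms is due to chance. This interval is not fixed then. It ends at delivery of the randomized intervention and contains the wait from randomization to placement. The protocol treats overlapping waiting time as an outcome elsewhere, so the same days can count both as a patient characteristic and as a result.

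Two things are at stake. First, a reader of the baseline table could take a difference in waiting time, caused by the allocation, for a failure of randomization. Second, the adjustment rule is triggered by imbalance, and the listed baseline variables are the natural place to look for it. If this interval entered the logistic model, the comparison of reinsertion would be conditioned on something the allocation can change.

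**Working it through.** **Order of events.** The sequence is consent, randomization, then primary placement by the allocated method. Write the listed interval as I = A + W, where A runs from surgery to randomization and W from randomization to placement. A is a true baseline quantity. W arises after allocation. The expected difference between arms in A is zero, so any systematic difference in I comes from W.

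**Overlap with the outcome.** If the physician's order precedes randomization, the order-to-placement time equals (order to randomization) + W. If the order follows randomization, the whole of it lies inside W. Either way the interval and the outcome share post-allocation waiting time.

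**Plan figures.** The point disputes no stated figure. The planning rates used below come from the Sample size calculation: "We estimate a success rate of 78% in the EM guided group versus 70% in the endoscopic group", that is, reinsertion of 22% and 30%, a difference of −8 points. With the 10-point margin and 80% power they reproduce the planned size at one-sided 0.05:

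n = (1.645 + 0.842)² × (0.78×0.22 + 0.70×0.30) / (0.08 + 0.10)² = 6.183 × 0.3816 / 0.0324 = 72.8, so 73 per arm. Then 73/0.95 = 76.8, so 77 per arm and 154 in total.

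**Illustration of the adjusted analysis.** These inputs are assumptions, not in the documents:
- A has mean 8 and SD 6 days.
- Endoscopy adds D = 0.5, 1 or 2 days to the wait.
- The log-odds of reinsertion change by β = 0, 0.02, 0.05 or 0.10 per day.

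Adjusting for I instead of A moves the arm coefficient by about β×D on the log-odds scale. On the risk scale this is about β×D×p(1−p), with p = (0.22 + 0.30)/2 = 0.26 and p(1−p) = 0.1924. Loss of the EM advantage in percentage points:

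| Extra wait D | β = 0 | β = 0.02 | β = 0.05 | β = 0.10 |
|---|---|---|---|---|
| 0.5 day | 0 | 0.19 | 0.48 | 0.96 |
| 1 day | 0 | 0.38 | 0.96 | 1.92 |
| 2 days | 0 | 0.77 | 1.92 | 3.85 |

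A logistic simulation with 400,000 patients per scenario agrees. For β from 0.02 to 0.10 it gives losses of about 0.2 to 1.0 points (0.5 day), 0.4 to 1.9 (1 day) and 0.8 to 3.8 (2 days). Risk differences in points at D = 1:

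| Scenario | Unadjusted | Adjusted for A | Adjusted for I |
|---|---|---|---|
| β = 0 | −8.00 | −8.00 | −8.00 |
| β = 0.05, reinsertion depends on A only | −7.88 | −7.87 | −6.93 |
| β = 0.05, reinsertion depends on all of I | −8.89 | −8.85 | −7.88 |

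In the second row the shift is plain bias. In the third, the wait is part of how allocation acts on reinsertion, and adjustment takes that part out. Adjusting for A alone leaves the risk difference essentially unchanged in every scenario.

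**The case against.** The strongest reply is that this is one mislabelled item in a descriptive list, and that the harm to the primary analysis is hypothetical. Much of that stands.

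- The Analyses section does not select this interval as a covariate or refer back to the baseline list. It speaks of possible confounders, and a variable changed by allocation is not a confounder, so a careful analyst could exclude it under the existing wording. An article commonly leaves the choice of covariates to the full protocol or analysis plan.
- No threshold for imbalance is given. A short difference in waiting may be lost in the variation of an interval that starts at surgery.
- No expected difference in delay is stated. Fasting and the move to another department make a longer wait for endoscopy plausible, but EM placement also needs a trained nurse, and patients needing placement at weekends or holidays are excluded from both arms.
- No data link the interval to reinsertion. Without such a link adjustment does no harm. If endoscopy waits longer and longer intervals go with more reinsertions, the shift is against EM, which is conservative for non-inferiority. An inverse relation would reverse it.

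A reader might infer that the plan does adjust for this interval and so removes part of the treatment effect, or that any difference in delay would trigger adjustment. The documents support neither: the covariates and the trigger are unspecified, and the two empirical conditions are unknown.

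None of this rescues the label. Calling the listed characteristics all pre-randomization is wrong for an interval that ends at the randomized procedure.

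**Conclusion.** The timing error is certain and follows from the article's own text. A possible consequence for the baseline table follows directly: if waiting time differs by arm, an effect of allocation would be shown as a chance imbalance.

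Bias in the primary comparison is a possibility, not something the plan prescribes. It needs three conditions together: a difference in waiting between arms, a relation between the interval and reinsertion, and selection of the interval as a covariate. The documents settle none of them, so neither size nor direction can be stated. Under the assumptions above, the shift ranges from nothing to 1.9 points for a one-day difference and to 3.8 points for two days, against a 10-point margin. For differences of a day or less it is probably small. The unadjusted intention-to-treat comparison and the sample size are unaffected. The correction is worth making because it is nearly free and closes off an avoidable ambiguity.

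**What to change.** 1. In Descriptive statistics, replace the item with the interval between surgery and randomization, reported for patients who had surgery. The Study population section also admits patients with conditions not requiring it.
2. In Analyses, state that the adjusted logistic model may include only variables fixed before randomization.
3. Leave the time from physician order to placement as the secondary outcome already specified. It needs no change.

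The cost is wording. The surgery date is already needed for the listed interval. The randomization date is not named as a data item, but allocation runs through a central online module and Trial status gives the date of the first randomization, so it should be available. With 133 of 154 patients randomized when Trial status was written, the change can be made before the final analysis without new data collection or a larger sample.

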#### Analyses

All analyses will be according to the intention-to-treat principles, meaning that all randomized patients are included in their initially assigned study arm, regardless of adherence to study protocol. The primary and secondary outcomes will be compared between the treatment groups. Results are presented as risk ratios with corresponding 95% confidence intervals. Except for the primary analysis of non-inferiority, a difference with a two-tailed P < 0.05 is considered statistically significant. In the event of imbalance between the two study arms a multivariable logistic regression will be used to correct for possible confounders. Additional as-treated and per-protocol analyses will be performed for the primary endpoint and the success rate of both tube placement methods.

A predefined subgroup analysis will be performed in patients with and without an altered upper GI anatomy after previous surgery. We will use logistic regression models to perform a formal test for interaction to assess whether outcomes differed significantly between these subgroups.

Interim analysis to evaluate serious adverse events and potentially prematurely terminate the study will not be performed, because of the perceived negligible risk associated with participation in this study.

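### The only effect measure named is a risk ratio with a 95% interval, but the 10% non-inferiority limit behind the sample size is an absolute 10 percentage points

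*Protocol article*

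**What the plan says.** Protocol article, Sample size calculation: the hypothesis is that "the need for reinsertion of a nasoenteral feeding tube after EM guided placement is at most 10% worse as compared to endoscopic placement". The design inputs are: "We estimate a success rate of 78% in the EM guided group versus 70% in the endoscopic group", where "Success is defined the absence of the need for reinsertion of an endoscope or tube". The result is: "When the non-inferiority limit is set at 10%, significance level at 0.05 and power at 80%, the sample size required per study arm is 73". Neither the scale of the 10% nor the sidedness of the 0.05 is written out.

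Protocol article, Analyses: after saying that primary and secondary outcomes will be compared between the groups, the section states: "Results are presented as risk ratios with corresponding 95% confidence intervals". The next sentence exempts the primary non-inferiority analysis from the two-sided 5% rule for significance, but gives no scale, interval level or decision rule in its place.

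The article names no risk difference, no risk-ratio limit and no conversion between the two.

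**The concern.** A non-inferiority conclusion rests on comparing a confidence limit with a margin, so both must be on the same scale. Here the margin behind the sample size is a difference in proportions, while the announced interval is for a ratio. Turning one into the other needs a control-group rate, and the equivalent ratio moves with that rate. It also depends on whether the ratio is formed for reinsertion or for its complement, success; the sample size section uses both.

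The trial's main conclusion is at stake. The same data can be called non-inferior on one scale and not on the other, and a sample size justified on the difference scale does not carry its power over to a ratio. The article also describes the trial as unblinded, which is a further reason to have the scale in writing before results are seen.

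**Working it through.** **Inputs** (Sample size calculation): success 78% EM guided and 70% endoscopic, so reinsertion 22% and 30%; limit 10%; significance level 0.05; power 80%. Allocation is 1:1 (Randomization).

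**1. Reproduce the 73 per arm.** On the difference scale, n = (z_α + z_β)² × [p₁(1−p₁) + p₀(1−p₀)] / (margin + expected advantage)².

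- Variance term: 0.78×0.22 + 0.70×0.30 = 0.3816. Distance: 0.10 + 0.08 = 0.18, squared 0.0324.
- One-sided 0.05: (1.645 + 0.842)² = 6.183; n = 6.183 × 0.3816 / 0.0324 = 72.8, so **73**. This matches.
- One-sided 0.025: (1.960 + 0.842)² = 7.849; n = 92.4, so 93. No match.

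Other readings of 10%, all at one-sided 0.05:

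| Reading of the limit | n per arm |
|---|---|
| Absolute 10 points | 73 |
| 10% relative on success (7 points) | 105 |
| 10% relative on reinsertion (3 points) | 195 |
| Ratio limit 0.90 on success, log scale | 97 |
| Ratio limit 1.10 on reinsertion, log scale | 222 |

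Only the absolute reading returns the stated figure. For the total, 146 / 0.95 = 153.7, so 154, which also agrees.

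**2. Translate 10 points into a ratio.** For reinsertion the equivalent is (p₀ + 0.10)/p₀; for success it is (1 − p₀ − 0.10)/(1 − p₀).

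| Endoscopic reinsertion rate p₀ | Reinsertion ratio | Success ratio |
|---|---|---|
| 20% | 1.50 | 0.875 |
| 30% (planned) | 1.333 | 0.857 |
| 40% | 1.25 | 0.833 |

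**3. Can the scales disagree?** Assume 73 per arm, 95% limits, and a ratio limit fixed at the planned 30% rate (1.333). The upper limit for the difference is d + 1.96 × √[p₁(1−p₁)/73 + p₀(1−p₀)/73]. For the ratio it is exp{ln(RR) + 1.96 × √[1/x₁ − 1/73 + 1/x₀ − 1/73]}.

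| Reinsertions, EM v endoscopic | Difference, upper limit | Below +10 points? | Ratio, upper limit | Below 1.333? |
|---|---|---|---|---|
| 16 v 22 (near planned rates) | +6.0 points | yes | 1.27 | yes |
| 12 v 15 | +8.5 points | yes | 1.59 | no |
| 33 v 36 | +12.1 points | no | 1.29 | yes |

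For 12 v 15: d = −0.041 and SE = 0.0642, so −0.041 + 0.126 = +0.085. RR = 0.80 and SE of the log = 0.350, so exp(−0.223 + 0.686) = 1.59. The success ratio for the same data (61 v 58) has a lower limit of 0.90, which passes 0.857. The two ratio forms therefore also disagree with each other.

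Sensitivity to the assumptions: with 90% limits, 12 v 15 still splits (+6.4 points; 1.42), while 33 v 36 passes on both (+9.5 points; 1.22). If the ratio limit is instead translated at the observed control rate, it is (0.2055 + 0.10)/0.2055 = 1.49 for 12 v 15, which 1.59 still fails at 95%. For 33 v 36 it is (0.4932 + 0.10)/0.4932 = 1.20, which 1.29 fails, in agreement with the difference.

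**4. Power at 73 per arm, planned rates.** On the difference scale, 0.18/√(0.3816/73) = 2.490. Subtracting 1.645 gives power 80%; subtracting 1.960 gives 70%. Against a reinsertion ratio of 1.333 the power is 68% at one-sided 0.05 (102 per arm needed for 80%) and 56% at one-sided 0.025 (130 needed).

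**The case against.** The strongest reply is that the quoted sentence concerns reporting. It says how results are presented, not how non-inferiority is tested. It cannot literally cover every outcome, since several secondary outcomes are continuous, and the sentence after it sets the primary analysis apart. A separate test on the risk difference is therefore compatible with the text, and a fuller protocol or analysis plan may contain one. The Discussion also gives the principle in words: the new method may be recommended if it is not worse than the limit. All of this stands. A reader might infer that the trial has no valid way to test its hypothesis, or that the scale will be chosen after the data are seen; the article supports neither.

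A reader might also take "is at most 10% worse as compared to endoscopic placement" as a relative limit, that is, a reinsertion ratio of 1.10. The article sets no such limit, and its own sample size rules that reading out.

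Finally, at about the planned rates (16 v 22) the difference and the translated ratio limit agree, so the divergent datasets lie away from the design assumptions. That is true, but the observed control rate may well differ from 30%, and the plan should not depend on its being close.

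What the reply does not remove is the mismatch between two things the article does state: the only measure named for the group comparisons is a ratio, and the limit is numerically a difference.

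**Conclusion.** The point holds as a mismatch between the reported measure and the scale of the margin. The sample size is right on its own inputs: 73 per arm and 154 in total both reproduce. But the interval announced for the primary outcome cannot be set against the 10-point limit without a control rate that the article does not fix for that purpose. The equivalent reinsertion ratio runs from 1.50 to 1.25 as that rate goes from 20% to 40%, and plausible results can be classified differently on the two scales.

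The interval level adds a second mismatch. The 73 per arm rests on one-sided 0.05, which corresponds to a 90% two-sided interval; judged by the stated 95% interval, power is about 70%.

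The conclusion assumes that the limit is absolute, which is inferred from the exact reproduction of 73, and the worked disagreements assume a ratio limit of 1.333 set at the planned 30% rate. It does not assume that a valid test is absent from documents not shown.

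**What to change.** Under Analyses, state: *The primary effect measure is the absolute risk difference in reinsertion (EM guided minus endoscopic). Non-inferiority is concluded if the upper limit of its two-sided 90% confidence interval (one-sided 0.05) lies below +10 percentage points. Risk ratios are given as supportive results.*

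If the 95% interval is to decide instead, say so and restate the power at 73 per arm as about 70%; 80% power would need 93 per arm before allowance for loss to follow-up.

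Under Sample size calculation, express the 10% limit as a reinsertion rate at most 10 percentage points higher, and give the 0.05 as one-sided.

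With the 90% interval this is a wording change: same data, same sample size. With the 95% interval the cost is either the admitted loss of power or more patients. Trial status reports 133 of 154 patients already randomized, so the statement should be made and dated before the outcome data are analysed.
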